## 1.0 Background

Health Care Transition (HCT) is a purposeful, planned process when youth progressively assume more responsibility for their health as they prepare to transfer from pediatric to adult care ^1,2^. Importantly, HCT should be informative and provide developmentally appropriate psychosocial support. ^1,2^. A poorly managed transition can have adverse effects on the quality and experience of care as well as contribute to poor disease outcomes including increased morbidity and even mortality ^1,3-7^. In fact, youth frequently report a negative experience during transition and as many as 50% disengage entirely from care ^4^. Despite knowing that the transition period is an extremely vulnerable time for youth with chronic disease, high quality research, evidence-based transition programs and consensus of what defines/determines a successful transition remain elusive ^8,9^.

While undergoing HCT, youth also experience critical life transitions that include changes to their biology (e.g., puberty), social networks (e.g., leaving parental home), and educational/vocational pursuits ^10,11^. Unfortunately, however, support for youth during this period (known as third phase of HCT - age 18-25) is often neglected in clinical care and is disproportionally under-researched ^2,8,12-17^ compared to earlier phases.

Health Coaching (HC) has been defined as “helping patients gain the knowledge, skills, tools and confidence to become active participants in their care so that they can reach their self-identified health goals” ^18^. For patients with early-stage kidney disease, HC demonstrated positive effects on quality of life, self-management, patient activation and self-efficacy after only six weeks of support and maintained its effects twelve weeks post intervention ^19^. While HC has been described as an adjunct form of support in rheumatology care ^20^, there is great potential for this role to collaborate with adult rheumatologists to optimally support youth after they transition to adult care.

The concept of HC was implemented at McMaster’s Young Adult Rheumatology Clinic in March 2020 in response to the COVID-19 pandemic. An ACPAC therapist supporting an adult rheumatologist ([name]) adapted service delivery by connecting virtually with each young adult one week prior to their appointment with the adult rheumatologist. This virtual meeting created dedicated time to provide the necessary education and support required in this third stage of HCT. Many stakeholders have noticed positive benefits of this program, including youth feeling more confident in their care, the adult rheumatologist noticing fewer ‘no shows’ and parents expressing relief that their children were well supported. As this positive feedback persisted, these sessions evolved further into individualized Health Coaching Interventions (HCI), guiding the young adults to gain knowledge, skills, tools and confidence while still providing medical care and supporting the young adults psychosocial, educational, and vocational needs during these virtual sessions.

## 2.0 Study Objectives

1. To assess the feasibility of conducting a multi-center, randomized-controlled trial to answer the following research question: To what extent does the implementation of a Youth Transition Roadmap (YTR) and virtual Transition Coach Intervention (TCI) improve self-management skills over the YTR alone in youth being transferred from pediatric to adult rheumatology care?
   1. The follow criteria will be used to assess feasibility: 1) Consent ≥85% of patients approached; 2) enroll ≥30% from non-primary site (London); 3) ≥90% attendance of virtual sessions; 4) complete ≥90% of outcome assessments at 8-month follow-up (TCI complete); and 5) have ≤5% missing data
2. To explore clinical outcomes at baseline, 8- and 11-months to characterize our study population and understand variability in changes over time in self-efficacy that may be used to power a large, multicentre RCT.

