## 3.3 Sample size

Our sample size is based on the more conservative of our two primary feasibility outcomes: ≥90% of TCI sessions attended. Assuming this, we will require a sample size of 97 for estimating the expected proportion with 6% absolute precision and 90% confidence ^21^. With an average of 7 patients transferring from pediatric to adult care each month (5 Hamilton, 2 London), we will approach 133 patients over 19 months. With an 85% consent rate ^22^ and a 90% study completion rate (133 x 85% x 90% = 102), we will ensure that we meet our sample target of 97 participants completing the study.

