# 4.0 Outcomes

This study is a pilot/feasibility study, which will be used to inform a multi-centre trial measuring the effect of transition coaching. The data required for the primary outcome includes rates of consent/recruitment, coaching session completion and data collection.

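### None of the five feasibility criteria is tied to the accrual plan, and London's share of enrolment, read naturally, is easier to reach when Hamilton under-recruits

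*Protocol*

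**What the plan says.** Protocol section 2.0 lists five criteria by which feasibility will be assessed. The first two read "Consent ≥85% of patients approached; 2) enroll ≥30% from non-primary site (London"). The remaining three ask that at least nine in ten coaching sessions be attended, that at least nine in ten of the 8-month assessments be done, and that no more than 5% of the data be missing.

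The accrual plan is in section 3.3. It expects 7 transferring patients a month, 5 at Hamilton and 2 at London, and states that "we will approach 133 patients over 19 months". With 85% consent and 90% completion it projects 102 completers against a target of 97.

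Section 4.0 describes the primary outcome data as including "rates of consent/recruitment, coaching session completion and data collection". Section 5.0 says that feasibility outcomes will be reported as counts and percentages. Neither section attaches a threshold to the number or rate recruited.

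**The concern.** The study exists to judge whether a multi-centre randomised trial can be run, and section 7.0 adds scaling to several centres. How many patients each site can enrol per month is central to that judgement. Yet the number recruited does not enter any of the five criteria. Each is a percentage of whoever was approached, enrolled or followed, so a shortfall in patient flow changes the precision of these percentages but not their expected values.

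Criterion 2 has a further problem. If it is London's share of all enrolled, it measures the balance between sites and not London's performance. It rises when Hamilton does badly, and on average it does not move when both sites fall short in the same proportion. Any cut-off on a share behaves this way, so this is separate from whether 30% is the right figure.

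**Working it through.** **Inputs.** From section 3.3: flow of 5 (Hamilton) and 2 (London) per month, 19 months, 85% consent, 90% completion, target 97. From section 2.0: consent at least 85%, London at least 30%.

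**The plan's own projection reproduces.** 7 × 19 = 133 approached; 133 × 0.85 = 113.05 enrolled; 113.05 × 0.90 = 101.7, stated as 102. By site at 85% consent: London 2 × 19 = 38 approached and 32.3 enrolled; Hamilton 95 approached and 80.8 enrolled.

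**Does any criterion use these numbers?** Criterion 1 is consented/approached. Criterion 2 is London enrolled divided by an unstated total. Criteria 3 to 5 are percentages of sessions, assessments and data. None contains 133, 113, 97, the monthly rate or the 19 months.

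**Expected London share**, L/(H + L), at 85% consent:

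| Hamilton / London per month | Enrolled | Completing (× 0.90) | London share |
| --- | --- | --- | --- |
| 5 / 2 (plan) | 113.0 | 101.7 | 28.6% |
| 4 / 2 | 96.9 | 87.2 | 33.3% |
| 2.5 / 2 | 72.7 | 65.4 | 44.4% |
| 1.5 / 2 | 56.5 | 50.9 | 57.1% |
| 2.5 / 1 | 56.5 | 50.9 | 28.6% |

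The share equals 30% when H = 2 × 0.70/0.30 = 4.67 per month. A Hamilton shortfall of 1 − 4.67/5 = 6.7% is therefore enough to move the expected share from below the criterion to the criterion. In the fourth row completers are 50.9/97 = 52% of target, while expected consent is still 85% and London's share is well above 30%.

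**Probability that criteria 1 and 2 are both met.** Simulation: number approached at each site is Poisson with the planned mean (an assumption; the protocol gives only averages), enrolled is binomial given approached, criterion 1 is enrolled/approached ≥ 0.85, and criterion 2 is London/all enrolled ≥ 0.30.

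| Scenario (London, Hamilton approached) | True consent 85% | True consent 90% |
| --- | --- | --- |
| On plan (38, 95) | 0.19 | 0.35 |
| Both at half flow (19, 47.5) | 0.21 | 0.36 |
| Only Hamilton at half flow (38, 47.5) | 0.51 | 0.93 |

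At 85% consent criterion 1 alone is met about half the time in every row (0.51 to 0.52), because its cut-off equals the assumed rate. Criterion 2 alone is met with probability 0.37, 0.40 and 0.99. So 0.51 in the third row is almost entirely the chance of meeting criterion 1.

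**If 30% means 30% of the planned total.** 0.30 × 113 = 33.9, so London would need 34. At 85% consent both criteria are then met with probability 0.24 on plan, below 0.001 with both sites at half flow, and 0.25 with only Hamilton at half flow. The advantage from a Hamilton shortfall all but disappears. Total accrual still has no threshold.

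**The case against.** The strongest reply is that accrual is not ignored. Section 4.0 collects recruitment rates, section 5.0 reports counts, section 3.1 documents ineligible patients and reasons, and section 3.3 gives a written benchmark by site. A shortfall would be visible. That stands, and it limits the point to this: a shortfall would be seen, but no stated criterion makes it count.

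A reader might infer that the trial could be declared feasible after missing its target by half. The protocol does not support that wording. Section 2.0 says the criteria will be used to assess feasibility; it states no rule that all must pass, no go/no-go decision and no formal verdict. Nor would half accrual make the first two criteria likely to be met: with both sites at half flow and 85% consent they are jointly missed about 79% of the time.

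The Hamilton effect depends on a denominator that criterion 2 does not state. On the planned-total reading it largely vanishes. London's share of those enrolled is the more natural reading, but the ambiguity is real.

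The figure of 0.93 should not lead. It rests on 90% true consent, where the protocol plans 85%, and on a scenario with about 69 completers, or 71% of 97. The documents also give no reason to expect Hamilton to halve while London stays on plan; section 7.0 says all pediatric rheumatology staff at that site are investigators.

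One might also argue that criterion 1 would miss a high ineligibility rate. Section 3.3 counts every transferring patient as approached, so on that usage ineligible patients stay in the denominator and criterion 1 would fall. The point here rests on reduced patient flow only.

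**Conclusion.** The concern holds in this limited form. The protocol itself fixes the list of feasibility criteria, and that list has no link to its own accrual plan even though recruitment is named as primary outcome data. Following the criteria as written can give a favourable assessment at about half the planned accrual, because none of them registers the shortfall.

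On the natural reading of criterion 2, under-recruitment at Hamilton helps: the expected London share goes from 28.6% to 44% at half flow there, and the probability of meeting criteria 1 and 2 together from about 0.19 to 0.51 at 85% consent. When both sites halve it is essentially unchanged (0.19 against 0.21). The shares follow from the protocol's figures by arithmetic. The probabilities also assume Poisson flow, equal consent at both sites and the share-of-enrolled reading.

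This is a weakness in how the criteria are built. It does not show that the trial will under-recruit.

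**What to change.** In section 2.0:

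- Add an accrual criterion anchored to the protocol's own target, for example at least 97 participants completing within the planned recruitment period and follow-up. On plan, completers have mean 101.7; under Poisson flow the chance of reaching 97 is about 0.69 at 85% consent and 0.86 at 90%. The sponsor should decide whether that margin is enough. If the 97 is revised for any reason, the criterion should follow it.
- Report enrolment per month, overall and by site, against the planned flow.
- Restate criterion 2 as London's enrolment against its own plan (38 approached, about 32 expected to enrol at 85% consent), and keep London's share as descriptive.
- Set the London pass mark below the expected value. With 113 overall and 32 for London as cut-offs, an on-plan trial at 85% consent would reach the first with probability about 0.51, the second with 0.54 and both with 0.37, so it would miss at least one about 63% of the time. As an illustration only, a London mark of 26 would be reached with probability 0.89 on plan (Poisson, mean 38 × 0.85 = 32.3) and about 0.02 at half flow (mean 16.15).

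The cost is protocol wording. Randomisation is already stratified by site (section 3.4) and enrolment counts arise in the ordinary running of the trial, so no further patients or procedures are needed. The downside is that the trial can now miss a criterion on accrual.

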# 3.0 Methods

This randomized-controlled feasibility trial will recruit patients over 19-months from 2 centers (Hamilton ON and London ON).

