## 3.4 Randomization

Consenting participants will be randomly allocated to the Transition Coach Intervention (TCI) or the control group using the Robust Randomization App ^23^ to generate a site-stratified computer-generated block randomization list with random varying permutated blocks of 4 and 6 and a 1:1 allocation ratio.

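### The feasibility threshold of 30% enrolment from London lies slightly above the 28.6% share that the protocol's own accrual figures imply

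*Protocol*

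**What the plan says.** Protocol section 2.0 lists five criteria for judging feasibility, which is the first objective. The first is "Consent ≥85% of patients approached". The second is "enroll ≥30% from non-primary site (London"), and it is the only one of the five that concerns the second site.

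Section 3.3 gives the accrual plan: "With an average of 7 patients transferring from pediatric to adult care each month (5 Hamilton, 2 London"), from which "we will approach 133 patients over 19 months". It then projects completers: "With an 85% consent rate ^22^ and a 90% study completion rate (133 x 85% x 90% = 102"). Each rate is a single figure applied to the combined total.

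Section 3.0 names two centres only. Section 3.4 specifies a "site-stratified computer-generated block randomization list", which balances the arms within each site and leaves the mix of sites unchanged. The protocol gives no London quota, no cap on Hamilton and no site-specific consent rate.

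**The concern.** A feasibility threshold should be one that a trial running to plan can be expected to meet. Here the threshold for London's contribution is higher than the contribution the accrual plan provides for. Because the criterion is a share, better consent at both sites does not help: if every patient approached at both sites agreed, London would still supply 2 in 7. With the stated patient flow, only higher consent in London than in Hamilton, or a chance departure from the 5:2 ratio, brings the share to 30%.

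At stake is how the trial's conclusion about multi-centre feasibility is read. London could recruit everything planned for it and the trial would still be recorded as missing the one criterion about the second site. Lowering the threshold after such a miss would not be credible.

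**Working it through.** **Inputs.** Section 3.3: 5 patients per month in Hamilton, 2 in London, 19 months, 85% consent, 90% completion. Section 2.0: London share of at least 30%. Assumption: the single consent rate applies equally at both sites, which is how section 3.3 uses it.

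**Reproducing the plan.** Approached: 7 × 19 = 133, of whom 5 × 19 = 95 in Hamilton and 2 × 19 = 38 in London. Completers: 133 × 0.85 × 0.90 = 101.7, stated as 102. The accrual figures reproduce.

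**Planned London share.**
- Approached: 38/133 = 2/7 = 28.6%.
- Enrolled: London 38 × 0.85 = 32.3; Hamilton 95 × 0.85 = 80.75; total 113.05; share 32.3/113.05 = 28.6%.
- The 90% completion rate also cancels, so the share among completers is the same.

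**Shortfall.** 30.0% − 28.6% = 1.4 percentage points. With 113 enrolled, 0.30 × 113 = 33.9, so 34 are needed against 32.3 expected. The expected count is below the required count at other totals too: 27.7 against 30 at 97, and 29.1 against 31 at 102.

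**What would close the gap.**
- Hamilton at 5 per month and equal consent: London needs 5 × 0.30/0.70 = 2.14 per month.
- Stated volumes and Hamilton consent at 85%: London needs (0.30/0.70) × 80.75 = 34.6 of 38, a consent rate of 91.1%.

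**Chance of meeting each threshold if the plan's rates are true.**

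| Accrual model | At least 30% | At least 25% |
|---|---|---|
| Binomial, 113 enrolled, probability 2/7 (34 or more; 29 or more) | 0.39 | 0.78 |
| Poisson enrolment, means 32.3 and 80.75 | 0.37 | about 0.8 |
| Exactly 38 and 95 approached, independent 85% consent | 0.20 | 0.98 |

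Under the binomial model, the chance of reaching 30% is 0.34 with 97 enrolled and 0.38 with 102. Missing the criterion is the more likely outcome in every case.

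**Sensitivity to rounding.** The protocol does not say whether 5 and 2 are rounded. If the true averages were anywhere in 4.5–5.5 and 1.5–2.5, London's share would lie between 1.5/7.0 = 21% and 2.5/7.0 = 36%.

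**The case against.** Several points can fairly be made for the protocol.

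- **The gap is about two participants, and the inputs are coarse.** The rates are whole-number averages, and London would need only 2.14 per month, which rounds to 2. This stands as a limit on severity. The stated figures are nevertheless the ones from which the protocol builds its 133, and it offers no others.
- **No decision rule is attached.** Section 2.0 says the criteria are used to assess feasibility, and section 5.0 reports feasibility outcomes as numbers and proportions, so readers will see London's actual count. This stands. Nothing in the randomization or the sample size depends on the threshold.
- **The denominator is not stated.** London's planned completers, 38 × 0.85 × 0.90 = 29.07, are 29.97% of the target of 97, so the 30% may have been set against that target. This is possible but unproven; the natural reading is a share of all enrolled. Reading it as 30% of London's own patients is strained, since that would be trivial beside the 85% consent criterion.
- **A low pass probability is not peculiar to this criterion.** The consent criterion is set exactly at the planned 85%, so it would be met with probability of only about 0.47 (at least 114 of 133). That is true. What is particular here is that the planned value lies below the threshold.

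A reader might also infer that the criterion rewards poor consent in Hamilton without anyone noticing. The documents do not support this. With London at 85%, the share reaches 30% if Hamilton falls to about 79% (75.4 of 95), but overall consent is then (75.4 + 32.3)/133 = 81%, and the first criterion fails.

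**Conclusion.** The inconsistency is real and small. On the protocol's own figures London is planned to supply 28.6% of those enrolled, against a threshold of 30%. A trial that accrues at its planned averages is therefore expected to miss the criterion by about two participants. This rests on equal consent at the two sites, on taking 5 and 2 per month at face value, and on reading the criterion as a share of all enrolled.

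A reader might conclude that the trial is bound to fail the criterion, or that such a failure would make the larger trial infeasible. Neither follows: chance alone would carry it past 30% in about 20% to 39% of cases, and the protocol does not say what missing one criterion of five entails. The point is a moderate-to-minor inconsistency in a stated threshold, worth correcting because the correction is easy and loses its value once results are known.

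**What to change.** Reconcile sections 2.0 and 3.3 before results are known, in one of two ways:

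1. Set the London threshold below 28.6% with a margin for chance, and name the denominator as all enrolled participants at both sites. At least 25% is one example; under the plan it would be met with probability of about 0.78 to 0.98.
2. Keep 30% and state in section 3.3 how London will supply more than 2 in 7 of those enrolled.

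A London target of 85% of those it approaches would not be a sound substitute. It requires 33 of 38 (32/38 is 84.2%), would be met with probability of only about 0.49 at a true 85% consent rate, and would no longer measure how much London contributes to the trial.

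The first option changes one line and needs no additional data; its cost is a slightly less ambitious threshold. The second needs a supporting accrual figure for London.

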# 5.0 Statistical Analysis

We will use frequencies (numbers and proportions) to report all feasibility outcomes related to Aim 1 including satisfaction questionnaires. Open-ended responses from participants and TCs will be used to inform modifications and refinement of the TCI for the fully powered study.

For Aim 2, descriptive statistics will summarize demographic characteristics and clinical outcomes at each time point. Baseline descriptors will also be summarized by sex and gender.

We will examine within-person, within-group and between-group changes in each PROMIS® outcome and will perform sub-analyses by sex and gender. We will determine means, medians, standard deviations and interquartile ranges as appropriate, at baseline and both follow-up times and calculate variability in changes over time. We will not perform statistical analyses of these changes or group differences as we are underpowered to detect them but will use these to calculate a sample size for a future fully powered study.

Data will be analysed using SPSS v.26 (IBM, New York, United States). Data analyses will be supervised by Drs. [name] and [name] who will support trainees in developing data analysis skills.

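### The 5% missing-data limit does not say whether unreturned assessments count; if they do, planned 90% retention meets criterion 4 but misses criterion 5, and the consent, attendance and London cut-offs have no margin over the plan and no interval

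*Protocol*

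**What the plan says.** Section 2.0 lists five criteria for judging feasibility, which is the trial's primary objective:

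- Criterion 1: "Consent ≥85% of patients approached".
- Criterion 2: "enroll ≥30% from non-primary site (London".
- Criterion 3: "≥90% attendance of virtual sessions".
- Criteria 4 and 5: "complete ≥90% of outcome assessments at 8-month follow-up (TCI complete); and 5) have ≤5% missing data".

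Criterion 5 gives no unit, denominator or time point.

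Section 3.3 supplies the planning values. It builds the sample size on "the more conservative of our two primary feasibility outcomes: ≥90% of TCI sessions attended" and says "we will require a sample size of 97 for estimating the expected proportion with 6% absolute precision and 90% confidence". Its accrual calculation uses 7 transfers a month (5 Hamilton, 2 London) for 19 months, 85% consent and "a 90% study completion rate (133 x 85% x 90% = 102".

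Section 5.0 states the reporting: "We will use frequencies (numbers and proportions) to report all feasibility outcomes related to Aim 1". It mentions no interval.

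**The concern.** There are two problems, and they are separate.

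**Criteria 4 and 5.** An assessment that never comes back can be read as missing data. On that reading the two criteria judge the same retention by different limits: 10% loss is acceptable under criterion 4 and too much under criterion 5. The protocol does not exclude this reading, so the same data could be reported as meeting or missing criterion 5 according to a choice made after the data are seen.

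**Cut-offs with no margin.** When a cut-off equals the expected rate, chance alone decides on which side the observed proportion falls. When it lies above the expected rate, as for London, a miss is the likelier result. A bare proportion does not show the reader how little separates the two outcomes. These proportions are what the future multicentre trial will be judged on.

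**Working it through.** **The plan's own figures**

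- Approached: 7 × 19 = 133 (95 Hamilton, 38 London).
- Completers: 133 × 0.85 × 0.90 = 101.7, about 102. This reproduces.
- Expected consents: 133 × 0.85 = 113.05, about 113. With 1:1 allocation, about 56 are in the TCI arm, giving 56 × 8 = 448 sessions.
- The 97 does not reproduce as stated. With n = z²p(1−p)/d², p = 0.90 and d = 0.06, 90% confidence gives 67.6, so 68; 95% confidence gives 96.04, so 97. That is a separate matter, and nothing below uses the 97.

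**Criteria 4 and 5 at 90% retention, with unreturned assessments counted as missing**

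| Reading of criterion 5 | Missing on plan | Retention needed for ≤5% | Chance of meeting it, n = 113 |
| --- | --- | --- | --- |
| 8-month assessments | 10% | 95% | P(at most 5 missing) = 0.03 |
| Pooled over baseline, 8 and 11 months | (0 + 10 + 10)/3 = 6.7% | 1 − 0.05 × 3/2 = 92.5% | P(at most 8 lost) = 0.19 |
| Items within returned forms | not given by the plan | no link to retention | not computable |

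The pooled row assumes a complete baseline and the same 10% lost at both follow-ups. The probabilities are binomial with a 10% loss rate. In the pooled row, 8 lost at two of three time points is 16/339 = 4.7%, and 9 lost is 18/339 = 5.3%. Criterion 4 itself needs at least 102 of 113, which has probability 0.54 if true 8-month completion is 90%.

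**Sensitivity to when the loss occurs.** The 90% in section 3.3 refers to study completion, and follow-up runs to month 11. If loss accrues evenly to 10% at month 11 (an assumption), loss at month 8 is 10% × 8/11 = 7.3%, so completion is 92.7%. Criterion 4 is then met with probability 0.88. Missing data is still 7.3% at 8 months, or (0 + 7.3 + 10)/3 = 5.8% pooled. Both remain above 5%.

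**The other cut-offs when the planning values are exactly true (exact binomial)**

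| Criterion | Cut-off | Planning value | Needed | Chance of meeting it |
| --- | --- | --- | --- | --- |
| 1 Consent | 85% | 85% | 114/133 (113/133 = 84.96%) | 0.47 |
| 2 London share | 30% | 2/7 = 28.6% | 34/113 | 0.39 |
| 3 Attendance | 90% | 90% | 404/448 sessions | 0.49 |

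The London row assumes equal consent at both sites. The attendance row treats sessions as independent. In a simulation of the same criteria, a within-person correlation of 0.3 left the chance at about one half (0.50).

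**Width of intervals near plan (exact 95%)**

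- Consent, 113/133: 78% to 91%.
- Completion, 102/113: 83% to 95%.
- London share, 32/113: 20% to 38%.

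**The case against.** The strongest reply is that criterion 5, listed after completion of assessments, most naturally means blank items in returned forms. Section 6.0 fits this, since it has completed questionnaires checked for completeness. On that reading there is no conflict. This stands as far as it goes: the conflict is conditional, and even on the wider reading both criteria can be met at higher retention. A reader might infer that criteria 4 and 5 contradict each other logically; they do not. But the narrower meaning is not written down, and the wider one cannot be squared with the retention the protocol plans for.

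A second reply is that 90% study completion need not equal 8-month completion. This is right. Criterion 4 should not be counted among the cut-offs that sit exactly on plan, and its chance of being met may be well above one half.

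Third, any cut-off is met about half the time when the truth lies on it. This is also right. It is no error in itself, but it is a reason to show the uncertainty. Banded decision rules that grant the top band whenever the estimate reaches the target would leave that chance unchanged, so they are a matter of preference.

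Fourth, intervals may be left to an analysis plan that is not shown, and section 5.0 does not exclude them. This limits the point on intervals to a mismatch inside the protocol: section 3.3 justifies the sample size by the precision of an interval, and section 5.0 names only numbers and proportions for the same outcome.

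**Conclusion.** The point holds in a limited form and is worth acting on.

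- If unreturned assessments count as missing, the planned 10% loss exceeds the 5% limit at 8 months (10%) and pooled (6.7%, or 5.8% if loss accrues evenly). Criterion 5, not criterion 4, would then set the retention standard, at about 95% or 92.5%. If only items in returned forms count, there is no conflict.
- The consent and attendance cut-offs equal their planning values, and the London cut-off lies 1.4 percentage points above its planning value (30% − 28.6%). Each is missed about half the time or more when the plan holds exactly.
- No interval is named for proportions whose 95% limits near plan span about 12 to 17 percentage points.

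A reader might go further and infer that a trial running to plan would probably fail its own feasibility test, by multiplying the chances across criteria. The protocol does not support that. Section 2.0 does not say that all five must be met, and section 3.3 speaks of two primary feasibility outcomes. A joint probability would rest on a rule the protocol does not contain, so none is given here.

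**What to change.** 1. In section 2.0, define criterion 5 as at most 5% of items missing within returned questionnaires, name the time points it covers, and leave unreturned assessments to criterion 4.
2. In section 5.0, report each feasibility proportion with a 95% confidence interval. For attendance, use a method that allows for up to 8 sessions from the same person.
3. Reconcile the 30% London cut-off with the 28.6% implied by the accrual figures in section 3.3, by changing one of them or by explaining how London is to exceed its expected share.
4. Optionally, say how the criteria will be combined, with or without intermediate bands. Bands would make the verdict less clear-cut in the middle range.

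The cost is a few sentences of protocol wording and a few extra lines of output. Sample size, visits and intervention do not change. Items 1 and 3 should be settled before feasibility results are seen.
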